
### Plans to promote participant retention and complete follow-up {18b}

Participants who deviate from the protocol are not withdrawn from the trial. Participants who withdraw from the trial nominate the degree to which they withdraw (i.e. whether they withdraw from active data collection ± passive data collection such as MBS/PBS data).

### Data management {19}

All participant characteristic and outcome data are entered directly into REDCap (Research Electronic Data CAPture – Vanderbilt University, hosted at Queensland University of Technology) by the research nurse ± the participants through self-administered online survey. To ensure data quality, the database is designed with branching logic, data validation, and range checks for data values, where possible.

All source data, clinical records, and laboratory data relating to the study will be archived at the clinical site as appropriate for 15 years after the completion of the study. All data will be available for retrospective review or audit. No study document will be destroyed without prior written agreement between the responsible organisation and the investigator. If the investigator wishes to assign the study records to another party or move them to another location, he/she must notify the responsible organisation in writing of the new responsible person and/or the new location.

### Confidentiality {27}

Data on potential participants is recorded, including reasons for ineligibility or refusal to participate. Participants are only identified by a unique participant study number on the case report forms and other study documents. Other study-related documents (e.g. signed consent form, participant log) are kept in strict confidence by the investigator.

Participants are informed that data is held on file by the responsible organisations and that these data may be viewed by staff including the study project manager and by external auditors on behalf of the responsible organisations and appropriate regulatory authorities (to include reviewing Human Research Ethics Committee (HREC) and the Research Governance Officers). Participants will be identified in publication and conference presentation reports only in aggregated form. All participant data will be held in strict confidence.

### Plans for collection, laboratory evaluation, and storage of biological specimens for genetic or molecular analysis in this trial/future use {33}

Not applicable. There is no collection of biological specimens in the current trial.

## Statistical methods

### Statistical methods for primary and secondary outcomes {20a}

Descriptive statistics will be used to report on feasibility and process-related elements (e.g. recruitment, intervention, retention rates) as well as clinical and resource outcomes. Preliminary effect size estimates for patient and resource use outcomes will be calculated following intention-to-treat principles using generalised linear mixed models. The distribution of the mixed models will be chosen as appropriate for the data, for example, a linear model for scale data or a Poisson for count data. Models will be adjusted for variables used in stratification of the randomisation process. Residuals of all models will be examined for statistical assumptions using descriptive statistics and plots.

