### Eligibility criteria {10}

The study population consists of patients with early-stage breast cancer (i.e. no-distant metastases) or ductal carcinoma in situ (DCIS). Patients will be eligible to participate from 2 weeks prior to completion of definitive treatment (surgery or adjuvant chemotherapy) and up to 18 months after completion of treatment. Patients meeting all of the following criteria are eligible for inclusion: diagnosis of curable, early breast cancer; receiving care at the Princess Alexandra Hospital; able to speak and read English; 18 years of age or older; ambulatory at the time of recruitment; Eastern Cooperative Oncology Group (ECOG) performance status 0 or 1; able to nominate a GP or GP clinic to be involved in their follow-up; and access to a telephone. Patients meeting any of the following criteria are excluded: presence of severe mental, cognitive, or physical conditions that would limit the patient’s ability to provide informed consent.

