### Participant timeline {13}

### Sample size {14}

In this pilot study, we will recruit 30 patients per arm in order to provide initial insights into the intervention feasibility and protocol as well as preliminary effect size estimates. The aim of this study is not hypothesis testing, and the power level is therefore not a valid consideration for sample size [28, 29]. The sample size for this study (*n* = 60) falls within the range of sample size recommendations for pilot studies of this nature [28, 29].

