## Assignment of interventions: allocation

### Sequence generation {16a}

Computer-generated random numbers are used to allocate participants in a 1:1 ratio by a researcher not involved in recruitment, intervention implementation, or data collection. Randomisation is blocked using random permuted blocks of eight and four to ensure that the groups are balanced periodically within stratification groups. Stratification groups include patients who have received (1) surgery only, (2) surgery and radiation only, (3) surgery and chemotherapy ± radiation and are Her2 negative, and (4) surgery and chemotherapy ± radiation and are Her2 positive. These stratification groups were chosen, with clinician input, to allow learnings for patients with different treatment pathways with different follow-up needs to inform the future definitive trial.

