### Implementation {16c}

Allocation sequence is generated by a researcher not involved in recruitment or data collection. Patients are enrolled by a research nurse who collects baseline data prior to randomisation. Enrolling nurses assign participants to the intervention after baseline data collection.

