### Methods in analysis to handle protocol non-adherence and any statistical methods to handle missing data {20c}

Preliminary effect size estimates for patient and resource use outcomes will be calculated following intention-to-treat principles using generalised linear mixed models. Patterns of missing data will be examined using chi-square and *t* tests. Missing data for the outcomes will be accounted for by using mixed models allowing the use of each available case by computing maximum likelihood estimates.

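### The effect-size models name only the randomisation strata for adjustment and do not commit to using the pre-randomisation score, which can cost precision at 30 per arm

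*Protocol article*

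**What the plan says.** Section {20a} of the protocol article plans generalised linear mixed models for the initial effect sizes and states the adjustment set: "Models will be adjusted for variables used in stratification of the randomisation process". Section {20c} adds that the mixed models handle missing outcomes by "allowing the use of each available case by computing maximum likelihood estimates". Neither section names another covariate, says whether baseline is a covariate or an outcome row, or identifies the contrast to be reported.

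The strata in section {16a} are four treatment pathways, beginning "Stratification groups include patients who have received (1) surgery only, (2) surgery and radiation only". None is a measure of quality of life or of any other outcome.

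A pre-randomisation score is available. Section {16c} says: "Patients are enrolled by a research nurse who collects baseline data prior to randomisation". Table 3 schedules FACT-B, diet, physical activity with sedentary behaviour, and financial toxicity at baseline and again during follow-up. Section {12} lists baseline among the timepoints of the FACT-B endpoint itself.

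On size and purpose, section {14} says "we will recruit 30 patients per arm in order to provide initial insights into the intervention feasibility and protocol", and gives initial effect-size estimates as a further purpose of the sample. It also says: "The aim of this study is not hypothesis testing, and the power level is therefore not a valid consideration for sample size".

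**The concern.** For a score measured repeatedly on the same patient, the baseline value is usually the strongest single predictor of the follow-up value. The article writes out an adjustment set and leaves that variable out of it. An analyst who follows section {20a} as written could fit a model with arm, time and stratum only, or a group-by-time model in which baseline is just another outcome row.

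The trial disclaims hypothesis testing, so the estimate and its interval are the quantitative output for patient outcomes, and the article says the results will inform a definitive trial. What is at stake is how much information 60 patients yield about effect size. It is not the validity of a test.

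**Working it through.** **The plan's own figure.** The sample size has no alpha, power, effect or SD behind it. All that can be reproduced is 2 × 30 = 60.

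**Inputs.**
- n = 30 per arm (section {14}); 1:1 allocation (section {16a}).
- Outcome SD set to 1, so results are in units of the residual SD within strata.
- r, the correlation between baseline and follow-up: not in the article. Assumed 0.3 to 0.7.
- Four timepoints (baseline, 3, 6 and 12 months) with compound symmetry, an assumption used only to check the repeated-measures models.
- 95% half-width = 2.002 × SE (t on 58 degrees of freedom). The one degree of freedom spent on a baseline slope is ignored.

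**Formulas for the arm difference at one follow-up time.**
- Baseline not used: SE = sqrt(2/n) = sqrt(2/30) = 0.258.
- Difference in change from baseline: SE = sqrt(4(1 − r)/n).
- Baseline as covariate: SE = sqrt(2(1 − r²)/n).

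| r | Not used: SE (half-width) | Change: SE (half-width) | Covariate: SE (half-width) | Unadjusted n per arm giving the covariate precision, 30/(1 − r²) |
|---|---|---|---|---|
| 0.3 | 0.258 (0.52) | 0.306 (0.61) | 0.246 (0.49) | 33 |
| 0.5 | 0.258 (0.52) | 0.258 (0.52) | 0.224 (0.45) | 40 |
| 0.7 | 0.258 (0.52) | 0.200 (0.40) | 0.184 (0.37) | 59 |

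**Covariate against no use of baseline.** The variance ratio is 1 − r², or 0.91, 0.75 and 0.51. The interval is narrower by 1 − sqrt(1 − r²), about 5%, 13% and 29%.

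**Covariate against change.** The variance ratio is (1 − r²)/(2(1 − r)) = (1 + r)/2. At r = 0.5 this is 0.75, a 25% saving; at r = 0.7 it is 0.85, a 15% saving. The interval is narrower by 1 − sqrt(0.75) = 13% and 1 − sqrt(0.85) = 8%.

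**Does a mixed model with baseline as an outcome row recover this unaided?** Generalised least squares at 30 per arm gives, for r = 0.3, 0.5 and 0.7:
- Group-by-time model, arm means free at baseline, arm difference at 12 months: SE 0.258, 0.258, 0.258. No gain.
- Same model, difference in change: 0.306, 0.258, 0.200, as in the table.
- Arm means constrained equal at baseline: 0.246, 0.224, 0.184. Identical to covariate adjustment.

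**Does this depend on looking at 12 months?** No. For the average over the three follow-up visits, the SE is 0.189, 0.211 and 0.231 with free baseline means, against 0.172, 0.167 and 0.144 with the constraint.

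**The case against.** The strongest reply is that the article nowhere says baseline is excluded. The sentence in section {20a} does not contain the word only, this is a condensed article, and a statistical analysis plan that is not shown may settle the matter. Baseline is one of the listed timepoints of the FACT-B endpoint, so the natural reading of a mixed model on all available cases already has baseline in it. If that model holds the arm means equal at baseline, the loss is zero. All of this stands. A reader might infer that the plan forbids baseline adjustment, and the text does not support that. It supports the narrower statement that the adjustment set is written out, baseline is not in it, and the one repeated-measures form that recovers the full precision is not stated.

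It is also fair to say that the study is about feasibility, that no decision rule depends on interval width, and that the correlation is an assumption. These limit the consequence but do not remove it, since effect-size estimates are a stated purpose of the sample.

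Four stronger readings are tempting and should be resisted:
- *Chance imbalance biases the estimate.* A baseline difference of one SE (0.258 SD) would move an unadjusted estimate by r × 0.258, or 0.13 SD at r = 0.5 and 0.18 SD at r = 0.7. This is random error already contained in the unadjusted SE (it is the r² share of the variance), so it is not a second harm.
- *Maximum likelihood makes the intervals too short.* Section {20c} describes how incomplete cases are used. It does not choose between full and restricted likelihood, and the article states no normal-based intervals.
- *Time since treatment must be a covariate.* Eligibility runs "up to 18 months after completion of treatment", but nothing in the article shows that this time predicts FACT-B once baseline is in the model.
- *The 12-month difference must be the main contrast.* That is a separate choice and does not follow from this point.

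**Conclusion.** The point holds as a missing commitment, not as an error in what is written. Section {20a} names the strata and does not commit to the pre-randomisation score. Under two ordinary readings of the model (baseline not used, or baseline as an outcome row with free arm means) the estimates are less precise than they need be.

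The half-width is 0.52 SD unadjusted against 0.49, 0.45 and 0.37 SD at assumed correlations of 0.3, 0.5 and 0.7. Against a change contrast the variance saving is 25% at 0.5 and 15% at 0.7. Under the constrained model there is no loss. These sizes rest on the assumed correlation, a linear model, equal variances and all 60 patients analysed. Loss to follow-up would widen every interval but leave the ratios the same.

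The point concerns outcomes with both a baseline and a follow-up value: FACT-B, diet, physical activity and sedentary behaviour, and financial toxicity. Satisfaction (12 months only) and resource use (after baseline only) are not affected. The consequence is imprecise planning estimates for the definitive trial. It is neither a biased comparison nor a threat to the feasibility objective.

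**What to change.** Add to section {20a}, and carry into any analysis plan: *Models for each outcome measured at baseline will include its pre-randomisation value as a covariate (or include baseline as an outcome with arm means constrained equal), in addition to the stratification factors.*

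The words pre-randomisation matter. Section {8} allows a further assessment before the Booster Nurse Clinic, which belongs to the intervention arm, and only the enrolment measurement should serve as the baseline value.

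The cost is one sentence, settled before the data are analysed. No extra data, visits or patients are needed. If an existing analysis plan already specifies either form, the article needs only to be read with it and nothing changes.

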### Interim analyses {21b}

Not applicable. No interim analysis is planned.

### Methods for additional analyses (e.g. subgroup analyses) {20b}

All qualitative interviews with participants assigned to the EMINENT intervention are audio-recorded and transcribed verbatim for analysis guided by the Consolidated Framework for Implementation Research [24].

### Methods in analysis to handle protocol non-adherence and any statistical methods to handle missing data {20c}

Preliminary effect size estimates for patient and resource use outcomes will be calculated following intention-to-treat principles using generalised linear mixed models. Patterns of missing data will be examined using chi-square and *t* tests. Missing data for the outcomes will be accounted for by using mixed models allowing the use of each available case by computing maximum likelihood estimates.

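### If the mixed models are fitted by full maximum likelihood as worded, standard errors for FACT-B and the other scale outcomes will be about 2-5% too small at n = 60

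*Protocol article*

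**What the plan says.** Three parts of the protocol article bear on this.

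- **Estimator.** The missing-data section {20c} plans generalised linear mixed models on intention-to-treat principles and says missing outcomes are handled by "allowing the use of each available case by computing maximum likelihood estimates".
- **Model family.** Section {20a} lets the distribution follow the data: "a linear model for scale data or a Poisson for count data". Models are adjusted for the randomisation strata. Sequence generation {16a} lists four strata, hence three indicator terms. FACT-B, the primary endpoint, is measured at baseline, 3, 6 and 12 months (Outcomes {12}).
- **Size and aim.** Under Sample size {14}, "we will recruit 30 patients per arm". The same section says that "The aim of this study is not hypothesis testing, and the power level is therefore not a valid consideration for sample size" and that the pilot is to give preliminary effect size estimates.

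These sections do not mention standard errors, confidence intervals, a confidence level, REML, a reference distribution or a degrees-of-freedom method.

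**The concern.** ML estimates variance components as if the fixed effects were known, so it makes no allowance for the degrees of freedom spent on estimating them. In a large trial this is invisible. With 60 patients, three stratum terms and arm-by-visit terms, the variance estimates are pulled down, and the standard error of the arm difference goes down with them. A normal quantile in place of a t quantile adds a little in the same direction.

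The point estimate of the arm difference is not the issue. What is affected is any statement of its precision, and the variance components themselves if they are carried into planning the definitive trial. As the pilot tests no hypothesis, precision statements would be its main quantitative inference on FACT-B.

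**Working it through.** There is no power calculation to reproduce. The stated total agrees with the arms: 2 × 30 = 60.

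**Inputs from the article:** n = 60, 1:1 allocation, four strata (three indicators), four visits, linear mixed model for scale data, ML.

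**Assumptions not in the article:** within-patient correlation 0.6, loss of 0% or 20%, equal strata, normal errors, nominal 95% intervals as estimate ± 1.96 × SE.

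**1. Closed form, one timepoint.** With p between-patient parameters, SE(ML)/SE(REML) = √((n − p)/n). Coverage of the ML interval with z is 2·T(1.96·√((n − p)/n)) − 1, where T is the t distribution function on n − p degrees of freedom.

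| Model, n = 60 | p | SE ratio | Coverage, ML with z | Widening to REML with t |
|---|---|---|---|---|
| Intercept, arm | 2 | √(58/60) = 0.983 | 0.941 | 1/0.963, 3.8% |
| plus 3 strata | 5 | √(55/60) = 0.957 | 0.934 | 1/0.936, 6.8% |
| plus baseline | 6 | √(54/60) = 0.949 | 0.932 | 1/0.927, 7.9% |

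The p = 2 row omits the planned strata and serves only as a lower bound. Baseline adjustment in the p = 6 row is an assumption.

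**2. Within-patient contrast, random intercept.** Four visits give 3 × 60 = 180 within-patient degrees of freedom, of which visit and arm-by-visit terms use 6: √(174/180) = 0.983, coverage 0.944. Contrasts in change from baseline are therefore less affected.

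**3. Simulated random-intercept model.** 60 patients, four visits, 11 fixed effects (4 visit means, 3 strata, 1 arm, 3 arm-by-visit), 2,000 runs per setting. A t quantile on 55 degrees of freedom stands in for a formal small-sample method.

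| 12-month contrast | Loss | SE ratio ML/REML | Coverage, ML with z | Coverage, REML with t |
|---|---|---|---|---|
| Difference in change | 0% | 0.983 | 0.940 | 0.945 |
| Difference in change | 20% | 0.980 | 0.946 | 0.954 |
| Difference in level | 0% | 0.965 | 0.941 | 0.955 |
| Difference in level | 20% | 0.965 | 0.944 | 0.954 |

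The Monte Carlo standard error of a coverage figure is about √(0.95 × 0.05/2000) = 0.005. The SE ratios are therefore the firmer evidence, and the 20%-loss coverages taken singly are not clearly below 0.95.

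**4. Simulated baseline-adjusted model, unstructured covariance, complete data.** 20,000 runs. Empirical SD of the estimate 0.2145; mean ML SE 0.2023; mean REML SE 0.2133; 0.2023/0.2133 = 0.948. Coverage is 0.930 (ML with z), 0.945 (REML with z) and 0.950 (REML with t). Most of the shortfall comes from ML (about 1.4 points) and the rest from z (about 0.5).

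**5. Scale.** The unadjusted 95% half-width at 30 per arm is 1.96 × √(2/30) = 0.51 SD. Understating it by 2-5% is 0.51 × 0.02 to 0.51 × 0.05, or about 0.01-0.03 SD.

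**The case against.** The strongest reply is that the sentence sits under missing data and explains why incomplete patients are kept. It does not set ML against REML for variance estimation. REML is also likelihood-based, and the choice between them is often left to an analysis plan, which is not shown here. This stands in part: the wording may be loose, and then the change is a clarification. But the article does name an estimator, and an analyst who follows it literally would fit full ML.

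Second, a reader might infer that the trial will report intervals that are too narrow. The article does not support that, because it promises no intervals and no normal quantiles. The coverage figures describe what would happen if intervals were formed that way.

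Third, a reader might quote a larger shortfall. The closed form with 48 patients (20% lost) and p = 6 gives 92.6%. That formula discards lost patients altogether, whereas the plan keeps their available visits, and it treats one timepoint in isolation. The repeated-measures simulations with 20% loss gave 94.4% and 94.6%. The lowest simulated figure, 93.0%, relies on an unstructured covariance and baseline adjustment that the article does not specify.

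Fourth, REML with Kenward-Roger is no blanket replacement. The phrase also covers the Poisson mixed models, to which standard REML does not carry over directly. Substituting it everywhere would leave the count outcomes without an estimation method. This stands, and the fix must be confined to the linear models.

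**Conclusion.** The point holds in conditional form and is minor. If the wording means full ML, standard errors for linear-model outcomes, FACT-B included, are about 2-5% too small at n = 60 with four strata, and a 95% interval using z would cover about 93-94.5%. The direction was the same in every setting examined. The size depends on the contrast (smaller for change from baseline than for level at 12 months), on the covariance structure, and on the assumed correlation and loss.

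The shortfall is far smaller than the sampling uncertainty at 30 per arm, and no feasibility conclusion is shown to turn on it. It does not extend to the count models. It is worth correcting because the stated reason for a likelihood method, use of every available case, is met equally well by REML.

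**What to change.** In section {20c}, separate the two model families:

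- **Linear mixed models (scale outcomes, including FACT-B):** restricted maximum likelihood with Kenward-Roger or Satterthwaite degrees of freedom. Keep the available-case rationale as it is.
- **Poisson mixed models (counts):** retain maximum likelihood and say so explicitly.

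The change takes a few words and a software option. It is not entirely free. Intervals for scale outcomes become about 4-8% wider (closed form, n = 60), and REML likelihoods cannot be used to compare models with different fixed effects, so any such comparison would need an ML refit.
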